### **7.6.2 Physical examination**

Physical examination must include a total body examination (general appearance, skin, neck, including thyroid, eyes, ears, nose, throat, lungs, heart, abdomen, back, lymph nodes, extremities and a basic nervous system neurological exam). Significant findings must be recorded either as Relevant Medical History / Current Medical Conditions (if present before treatment) or as Adverse Events (if newly occurring or worsening since starting treatment).

### **7.6.3 Vital signs**

Pulse, respiratory rate, blood pressure and temperature, and height (screening visit only) and weight will be measured as indicated in the evaluation schedule ([Table 7-1](#) and [Table 7-2](#)) and will be recorded on source documents and entered on the Vital Signs CRF pages. Blood pressure, pulse and respiratory rate should be measured on patients after at least 3 minutes in the sitting position.

### **7.6.4 WHO performance status and scale**

WHO performance status will be measured as indicated in the assessment schedules ([Table 7-1](#) and [Table 7-2](#)).

### **Performance Status WHO grade:**

- Grade 0: Fully active, able to carry out all normal activity without restriction.
- Grade 1: Restricted in physically strenuous activity but ambulatory and able to carry out work of a light or sedentary nature, e.g., light house work, office work.
- Grade 2: Ambulatory and capable of all self-care but unable to carry out any work activities. Up and about more than 50% of waking hours.
- Grade 3: Capable of only limited selfcare, confined to bed or chair more than 50% of waking hours.
- Grade 4: Completely disabled. Cannot carry on any self-care. Totally confined to bed or chair.
- Grade 5: Dead

### **7.6.5 Laboratory evaluations**

All standard clinical laboratory analyses described below are to be performed by the central laboratory, according to the Visit Schedule outlined in [Table 7-1](#). The name of the central laboratory can be found in the investigator binder supplied to the site. Details about all central laboratory procedures including collection, shipment of samples, reporting of results and alerting of extreme values are given in the manual provided by the central laboratory. Notable values will be provided in the [Laboratory Manual].

For clinically relevant laboratory values from local labs, the actual laboratory value should be recorded on the Local Lab CRFs and local lab ranges should be provided on the Lab Normal Range sheet as appropriate. Unscheduled abnormal laboratory evaluations which are clinically relevant (e.g., require dose modification and/or interruption of study drug, indicate changes in previously abnormal values) must be recorded on the Adverse Events CRF.

Screening safety laboratory tests (hematology, biochemistry, lipid profile, urinalysis and coagulation) will need to be repeated at Treatment Day 1 if they were collected more than 14 days prior to Treatment Day 1. For the week 6 visit (visit 5 in the blinded portion and visit 105 in the open label/extension portion), patients residing in the United States for whom travel is difficult, who have tolerated study medication and have no adverse events may, at the discretion of the investigator, attend a local laboratory affiliated with EXAM **One** for blood draws (if such facility is available) and have a telephone consultation with the investigator rather than a clinic visit (detailed instructions are provided in the [Quest Diagnostic Laboratory Manuals]).

Patients will be advised to fast on the days of scheduled visits prior to blood sampling period (note: patients are allowed to consume water during this time). A light breakfast may be taken after this point, prior to trial therapy administration, however, patients should be advised to avoid fatty meals.

#### **7.6.5.1 Hepatitis screen**

Patients who have a positive test for Hepatitis B or C at screening must be excluded from the study. Please note that patients who test negative for HBV-DNA, HBsAg, and HBcAb but positive for HBs Ab, due to prior history of vaccination against Hepatitis B will be eligible. The fact that the patient had been vaccinated should be entered into the patient's Medical History CRF. Hepatitis testing will be done only at screening (see [Table 7-1](#)) for patients that

meet the criteria outlined in [Section 4.1](#). Guidelines for those patients that have already been randomized prior to the approval of [Amendment 1.5.1](#) are detailed in [Table 4-1](#) and [Table 4-2](#).

If an already randomized patient (at the time of Amendment 1 approval) tests positive for Hepatitis C, and the criteria for reactivation according to [Table 4-3](#) are observed, the patient should discontinue study treatment. Please refer to [Table 7-1](#) and [Table 7-2](#) for HCV RNA-PCR monitoring schedule for those patients with positive HCV RNA-PCR, baseline tests who have not yet met the reactivation criteria outlined in [Table 4-3](#).

#### **7.6.5.2 Hematology**

Hematology tests will be performed at each scheduled visit as indicated in [Table 7-1](#) and [Table 7-2](#). The hematology profile must include: hemoglobin, hematocrit, platelets, red blood cell count (RBC), total white blood cell count (WBC) absolute & differential (including neutrophils, lymphocytes, monocytes, eosinophils, basophils). Absolute neutrophil count (ANC) will be calculated by the central laboratory.

#### **7.6.5.3 Coagulation**

Prothrombin time (PT) will be determined at screening and every 12 weeks after the start of study treatment; it will be reported as international normalized ratio (INR). In addition, fibrinogen and partial thromboplastin time (PTT) will be determined at screening and every 12 weeks after the start of study treatment. The amount of blood to be drawn for these assessments can be found in the central [Laboratory Manual].

#### **7.6.5.4 Biochemistry and lipid profile**

Biochemistry tests including serum lipid profile will be performed at each scheduled visit as indicated in [Table 7-1](#) and [Table 7-2](#): sodium, potassium, chloride, bicarbonate, creatinine, albumin, total protein, SGOT (AST), SGPT (ALT), total bilirubin, alkaline phosphatase, uric acid, BUN, calcium, magnesium, phosphate, total LDH, and fasting glucose. Please refer to the central [Laboratory Manual] for the amount of blood to be drawn for these assessments at each visit.

In order to assess renal function during the trial, the Cockcroft-Gault formula will be used. The Cockcroft-Gault formula is shown below, where creatinine clearance is “x” (in mL/min), age is measured in years, weight in kg, creatinine in µmol/L, and the constant is 1.23 for men and 1.04 for women ([Cockcroft et al 1976](#)):

$$x = \frac{(140 - \text{age}) \times \text{weight} \times \text{constant}}{\text{creatinine}}$$

A lipid profile (cholesterol, triglycerides, LDL, HDL) will be determined at screening and repeated every 12 weeks while receiving study drug (at 12 and 24 weeks and every 12 weeks thereafter). The amount of blood to be drawn for this assessment is listed in. The patient must be in a fasting state at the time of blood sampling for this evaluation.

#### **7.6.5.5 Urinalysis**

During screening, a standard urinalysis (pH, protein, glucose, blood, ketones, and leukocytes) should be performed and submitted to the central laboratory. Urine dipstick will be performed

routinely thereafter at each study visit (excluding visits 2, 3 and 5). This must be supplemented with central laboratory quantification of any potentially relevant abnormalities.

#### **7.6.5.6 Pregnancy test**

All females of child-bearing potential must have a negative serum pregnancy test at screening/baseline as well as a negative urine pregnancy test (performed locally) prior to treatment on Treatment Day 1. Urine pregnancy tests will then be repeated every 4 weeks until discontinuation of study drug. A serum pregnancy test will be performed at either the end of treatment or end of study visit (depending upon the reason why the patient has discontinued study medication). Patient should be instructed to inform site of a positive urine pregnancy result. Repeat serum pregnancy testing will be performed for confirmation of a positive urine pregnancy test. It is recommended that postmenopausal women be amenorrheic for at least 12 months or have a serum follicle-stimulating hormone (FSH) of >40 mIU/ml to be considered “of non-childbearing potential” or 6 weeks post surgical bilateral oophorectomy with or without hysterectomy.

**Highly effective contraception must be used on-study and for up to 8 weeks after ending treatment (definition of highly effective contraception is detailed in [Section 7.3.1.1](#)).**

#### **7.6.5.7 Reproductive history and endocrine testing**

In order to provide additional follow-up on cases of amenorrhea, increased hormonal evaluation will be performed and supplemental medical history will be collected.

Additional menstrual history (age at menarche, previous cases of amenorrhea or menstrual disorders, biological mother’s age at menopause) and pregnancy history (pregnancies, full-term gestations, abortions, live births, miscarriages) will be collected one time after implementation of protocol amendment 3. Following implementation of amendment 3, menstrual status will be collected monthly via patient diary. Every 12 weeks, data from patient diary will be collected at clinical site for CRF. It is recommended that study coordinators contact patients monthly for the first 3 months to remind patients to document menstrual status in patient diary.

A blood sample for analysis of total testosterone, FSH and LH (all patients) and estradiol (female patients) will be obtained at the screening/baseline visit and every 12 weeks after the start of study drug. In the event that amenorrhea is reported in between scheduled assessments, hormone evaluations should be completed at that time.

For patients who did not have the endocrine parameters tested, there will be no retrospective analysis of blood samples.

### **7.6.6**

#### **7.6.7 Electrocardiogram (ECG)**

A standard 12-lead ECG is to be performed at screening/baseline and at end of treatment. Tracings must be dated and signed by the investigator (or his/her designee) and filed with the subject’s source documentation. Results from 12-lead ECG should be captured on the ECG Evaluation CRF. Significant findings must be recorded as Relevant Medical History / Current

Medical Conditions (if present before treatment). ECG may be repeated at the discretion of the investigator at any time during the study and as clinically indicated; any clinically relevant findings should be recorded on the Adverse Events CRF.

## 7.7 Pharmacokinetics

Biofluid concentrations will be expressed in mass per volume units. All concentrations below the limit of quantification or missing data will be labeled as such in the concentration data listings. Concentrations below the limit of quantification will be treated as zero in summary statistics.

Patients will be advised to fast overnight on the days of blood sampling for RAD001 prior to the sampling period (note: patients are allowed to consume water during this time). A meal may be taken after the pre-dose sample has been collected, but prior to ingestion of the daily RAD001 dose; patients should be advised to avoid fatty meals.

### 7.7.1 Pharmacokinetics blood sample collection and handling

During the blinded treatment phase of the study, pre-dose trough blood samples for determination of RAD001 concentration ( $C_{min}$ ) will be collected immediately prior to dosing at weeks 2, 4, 12, 24 and 48. **A trough blood sample is defined as a sample of blood collected 22-26 hours for daily dosing (or 46-50 hours for every other day dosing) after the patient's last dose of study drug, following 5 days of consistent (daily dose and timing of dose) dosing.** In addition to trough blood samples, a PK blood sample (2 mL) will be taken 2 h ( $\pm$  30 mins,  $C_{2h}$ ) after trial therapy dose administration at weeks 2, 4, 12, 24 and 48. Pre-dose trough ( $C_{min}$ ) and 2 h ( $\pm$  30 mins,  $C_{2h}$ ) blood samples will be collected in both treatment arms by either direct venipuncture or an inserted indwelling cannula. Please refer to [Table 7-5](#) for amount of blood to be drawn for each trough ( $C_{min}$ ) and 2 h ( $\pm$  30 mins,  $C_{2h}$ ) PK assessment and the PK sample number that should be assigned to each sample.

For the 6 week visit (visit 5 in the blinded portion and visit 105 in the open label/extension portion), patients residing in the United States for whom travel is difficult, who have tolerated study medication and have no adverse events may, at the discretion of the investigator, attend a local laboratory affiliated with EXAM One for blood draws (if such facility is available) and have a telephone consultation with the investigatory rather than a clinic visit (detailed instructions are provided in the [Quest Diagnostics Laboratory Manual]).

**Table 7-5 PK sample log table**

| Study Day | Study Week | Time                | PK Collection Number | PK Sample Number | Sample Volume (mL) |
|-----------|------------|---------------------|----------------------|------------------|--------------------|
| Day 14    | Week 2     | Pre-dose            | 101                  | 101              | 2 mL               |
| Day 14    | Week 2     | 2 h ( $\pm$ 30 min) | 1                    | 201              | 2 mL               |
| Day 28    | Week 4     | Pre-dose            | 102                  | 102              | 2 mL               |
| Day 28    | Week 4     | 2 h ( $\pm$ 30 min) | 2                    | 202              | 2 mL               |
| Day 84    | Week 12    | Pre-dose            | 103                  | 103              | 2 mL               |
| Day 84    | Week 12    | 2 h ( $\pm$ 30 min) | 3                    | 203              | 2 mL               |
| Day 168   | Week 24    | Pre-dose            | 104                  | 104              | 2 mL               |
| Day 168   | Week 24    | 2 h ( $\pm$ 30 min) | 4                    | 204              | 2 mL               |
| Day 336   | Week 48    | Pre-dose            | 105                  | 105              | 2 mL               |

|         |         |                |   |     |      |
|---------|---------|----------------|---|-----|------|
| Day 336 | Week 48 | 2 h (± 30 min) | 5 | 205 | 2 mL |
|---------|---------|----------------|---|-----|------|

### Blood sample collection

A 2 mL sample of venous blood will be drawn for RAD001 blood concentration determination from a forearm vein into tubes containing EDTA. The tube will be inverted several times to mix contents (e.g., anti-coagulant) immediately after collection of the blood sample. Prolonged contact must be avoided with rubber stopper. The whole blood sample will be transferred to a labeled polypropylene screw cap tube and frozen at - 20°C or below within 60 minutes of venipuncture. An example of the label that should be attached to the tube is shown below. The respective PK sample number shown in Table 7-5 should be entered on each label next to “sample number”.

PK labels will be designed as follows:

|                             |                      |
|-----------------------------|----------------------|
| Study number                | CRAD001M2302         |
| Subject initials and number | ____ / _____ - _____ |
| Analyte                     | Everolimus           |
| Sample number               | ____                 |

### Sample collection handling

The actual collection time of all samples must be documented on the PK Blood Collection CRF pages. **The date and actual time of the last dose of study drug and date and time of the dose of study drug taken on the day of the sampling must be recorded on the PK Blood Collection CRF. In addition, dates and times of blood samplings must be entered on the PK Blood Collection CRF.** Any sampling problems (i.e., patient took study drug before a trough [pre-dose]) must be noted in the comments section of the CRF.

In order to assure compliance with sampling procedures, **on days of drug level and PK assessment, drug administration should be supervised by study center personnel.**

If the patient's dose has been interrupted for more than 48 hours prior to when a PK blood collection is required, it is not necessary to collect the PK sample. If the patient vomits within the first 4 hours following study-drug administration on the day of PK blood sampling, the time (using the 24-hour clock) of vomiting should be recorded on the PK Blood Collection CRFs. No additional study drug should be taken that day to replace the dose that was vomited.

#### 7.7.2 Pharmacokinetic sample shipment

All blood samples must be carefully packed in suitable packing material containing sufficient dry ice to keep them frozen during shipment.

A list of all samples, including the date, subject number, and time of sampling should be sent with the shipment. Any missing samples should be noted on the list.

Samples will be sent to Quest Diagnostics Clinical Trials Labs [name]. Shipments should all be sent on Monday, Tuesday, or Wednesday, using a carrier guaranteeing overnight delivery (e.g., World Courier).

Please refer to the [Laboratory Manual] for specific sample shipment information.

### 7.7.3

## 7.8 Biomarkers

Biomarker studies are proposed using patient's plasma samples. These studies will focus on measuring the effect of RAD001 on soluble markers of angiogenesis. mTOR inhibitors have been shown to have an inhibitory effect on tumor growth and angiogenesis both *in vitro* and *in vivo*. VEGF and its family members are essential mediators of tumor angiogenesis. We plan to examine the effects of RAD001 on tumor vascularization through the measurement of these angiogenic growth factors and their corresponding soluble receptors. Data from these studies will be used to formulate hypotheses for future studies of RAD001 as an anti-angiogenic agent.

Patients will be asked to donate 3 mL of blood for plasma analysis at the following time points (also refer to [Table 7-1](#)) unless local or national regulations do not permit:

- screening/baseline
- 4 weeks
- 12 weeks
- 24 weeks
- 36 weeks
- 48 weeks
- End of Treatment

The blood samples for biomarker assessments should be collected immediately prior to study drug administration. On-treatment samples will be compared to baseline samples for RAD001 effects on plasma angiogenic molecules, e.g., basic FGF, VEGF, PLGF, soluble VEGF receptor1 and soluble VEGF receptor2. Exploratory assessments

### 7.8.1

## 8 Safety monitoring

### 8.1 Serious adverse event reporting

To ensure patient safety, every SAE, **regardless of suspected causality**, occurring after the patient has provided informed consent and until 4 weeks after the patient has stopped study treatment/participation must be reported to Novartis within 24 hours of learning of its occurrence. Any SAEs experienced after this 4-week period (**for up to 12 weeks (84 days)**) should only be reported to Novartis if the investigator suspects a causal relationship to the study drug. Recurrent episodes, complications, or progression of the initial SAE must be reported as follow-up to the original episode within 24 hours of the investigator receiving the follow-up information. An SAE occurring at a different time interval or otherwise considered completely unrelated to a previously reported one should be reported separately as a new event.

Information about all SAEs is collected and recorded on the Serious Adverse Event Report Form. The investigator must assess and record the relationship of each SAE to each specific

study drug (if there is more than one study drug), complete the SAE Report Form in English, and send the completed and signed form by fax within 24 hours to the local Novartis Integrated Medical Safety.

The telephone and fax number of the contact persons in the local department of Pharmacovigilance Operations, specific to the site, are listed in the investigator folder provided to each site. The original copy of the SAE Report Form and the fax confirmation sheet must be kept with the CRF documentation at the study site.

Follow-up information is sent to the same person to whom the original SAE Report Form was sent, using a new SAE Report Form stating that this is a follow-up to the previously reported SAE and giving the date of the original report. Each recurrence, complication, or progression of the original event should be reported as a follow-up to that event regardless of when it occurs. The follow-up information should describe whether the event has resolved or continues, if and how it was treated, whether the blind was broken or not, and whether the patient continued or withdrew from study participation.

If the SAE is not previously documented in the current version of the [Investigator's Brochure], or Package Insert (new occurrence) and is thought to be related to the Novartis study drug, a Novartis Pharmacovigilance Operations or Integrated Medical Safety associate may urgently require further information from the investigator for Health Authority reporting. Novartis may need to issue an Investigator Notification (IN), to inform all investigators involved in any study with the same drug that this SAE has been reported. Suspected Unexpected Serious Adverse Events will be collected and reported to the competent authorities and relevant ethics committees in accordance with Directive 2001/20/EC or as per national regulatory requirements in participating countries.

## **8.2 Pregnancies**

To ensure patient safety, each pregnancy in a patient on study drug must be reported to Novartis within 24 hours of learning of its occurrence. The pregnancy should be followed up to determine outcome, including spontaneous or voluntary termination, details of the birth, and the presence or absence of any birth defects, congenital abnormalities, or maternal and/or newborn complications.

Pregnancy should be recorded on a Clinical Trial Pregnancy Form and reported by the investigator to the local Novartis Integrated Medical Safety Department. Pregnancy follow-up should be recorded on the same form and should include an assessment of the possible relationship to the Novartis study drug of any pregnancy outcome. Any SAE experienced during pregnancy must be reported on the SAE Report Form.

Pregnancy outcomes must be collected for the female partners of any males who took study drug in this study. Consent to report information regarding these pregnancy outcomes should be obtained from the mother.

Preclinical data regarding reproductive toxicity is described in the most recent [Investigator Brochure]. The potential reproductive risk for humans is unknown.

Women of childbearing potential should be advised to use highly effective contraception methods while they are receiving everolimus and up to 8 weeks after treatment has been stopped.

If a pregnancy occurs while on study treatment, the newborn will be followed for at least 12 months.

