## 5.1 Inclusion criteria

1. Male or female  $\geq 18$  years of age.
2. Clinically definite diagnosis of tuberous sclerosis according to the modified Gomez criteria ([Roach 1998](#), [Hyman 2000](#), [Table 5-1](#)) **or** sporadic LAM (biopsy-proven or compatible chest CT scan). Clinically definite diagnosis of tuberous sclerosis according to the modified Gomez criteria is defined as either of the following:
  - Two Major Features from Table 5-1.
  - One Major Feature plus two Minor Features from [Table 5-1](#).
3. Clinically definite diagnosis of renal angiomyolipoma.
4. Presence of at least one angiomyolipoma  $\geq 3$  cm in its longest diameter using CT/MRI.
5. If female and of child-bearing potential, documentation of negative pregnancy test prior to enrollment. Sexually active pre-menopausal female patients (and female partners of male patients) must use highly effective contraceptive measures, while on study and for 8 weeks after ending treatment.
6. Written informed consent according to local guidelines.

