### **7.3.1 Special laboratory tests**

#### **7.3.1.1 Pregnancy test**

Women of child-bearing potential, defined as all women physiologically capable of becoming pregnant, must use highly effective contraception during the study and for 8 weeks after stopping treatment. Highly effective contraception is defined as either:

- Total abstinence: When this is in line with the preferred and usual lifestyle of the subject. (Periodic abstinence (e.g., calendar, ovulation, symptothermal, post-ovulation methods) and withdrawal are not acceptable methods of contraception)

- Sterilization: have had surgical bilateral oophorectomy (with or without hysterectomy) or tubal ligation at least six weeks before taking study treatment. In case of oophorectomy alone, only when the reproductive status of the woman has been confirmed by follow up hormone level assessment
- Male partner sterilization (with the appropriate post-vasectomy documentation of the absence of sperm in the ejaculate). (For female subjects on the study, the vasectomised male partner should be the sole partner for that subject)
- Use of a combination of any two of the following (a+b or a+c or b+c):
  - a. Use of oral, injected, implanted or other hormonal methods of contraception
  - b. Placement of an intrauterine device (IUD) or intrauterine system (IUS)
  - c. Barrier methods of contraception: Condom or Occlusive cap (diaphragm or cervical/vault caps) with spermicidal foam/gel/film/cream/vaginal suppository
- In case of use of oral contraception women should have been stable on the oral agent before taking study treatment.

Sexually active males must use a condom during intercourse while taking the drug and for 8 weeks after stopping treatment and should not father a child in this period.

A condom is required to be used also by vasectomised men in order to prevent delivery of the drug via seminal fluid.

Female partners of male patients must also be advised to use one of the following contraception methods: Use of (1) oral, injected, implanted or other hormonal methods of contraception, or (2) intrauterine device (IUD) or intrauterine system (IUS), or (3) prior male/female sterilization.

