A serum pregnancy test must be completed within 14 days of randomization and a urine pregnancy test follow-up completed prior to randomization on Treatment Day 1. Female patients who are able to become pregnant will have a repeat urine pregnancy test every 4 weeks while receiving study drug until study drug discontinuation. Pregnancy testing is required at screening and monthly until the end of the study (core and extension). Serum pregnancy testing should be performed at screening and at either the end of treatment or the end of the study (depending upon the reason why the patient discontinued study medication). Urine pregnancy testing will be performed every 4 weeks at the patient's home or at clinical site when a visit is scheduled. Urine pregnancy test will be conducted at clinical site in place of patient's home when a visit is scheduled.

Patient should be instructed to inform site of a positive urine pregnancy result. Repeat serum pregnancy testing will be performed for confirmation of a positive urine pregnancy test.

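### Section 8.2 ties patient pregnancy reporting and newborn follow-up to time on drug, leaving out the protocol's own 8-week post-treatment contraception period

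*Protocol*

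**What the plan says.** **Contraception.** Inclusion criterion 5 (section 5.1) says that sexually active pre-menopausal women and female partners of male patients "must use highly effective contraceptive measures, while on study and for 8 weeks after ending treatment". Section 7.3.1.1 says that women of child-bearing potential "must use highly effective contraception during the study and for 8 weeks after" treatment stops. Male patients have a condom rule that runs "for 8 weeks after stopping treatment and should not father a child in this period". Section 8.2 itself advises "highly effective contraception methods while they are receiving everolimus and up to 8 weeks after treatment has been stopped", and says that the potential reproductive risk in humans is unknown.

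**Reporting and newborn follow-up.** Section 8.2 requires that "each pregnancy in a patient on study drug must be reported to Novartis within 24 hours of learning of its occurrence". On the child it says: "If a pregnancy occurs while on study treatment, the newborn will be followed for at least 12 months". For female partners, outcomes are to be collected for any male who took study drug, with the mother's consent and no reference to whether he was still taking it.

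**Testing.** Section 7.6.5.6 says: "Urine pregnancy tests will then be repeated every 4 weeks until discontinuation of study drug". Section 7.3, section 7.3.1.1 and the pregnancy-test footnotes to Tables 7-1 and 7-2 have the same end point. Section 7.3.1.1 also says: "Pregnancy testing is required at screening and monthly until the end of the study (core and extension". A serum test is due at either end of treatment or end of study, depending on the reason for stopping.

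**The concern.** The protocol asks patients to avoid pregnancy for 8 weeks after the last dose, but its reporting and newborn rules for patients stop at the last dose. A site that follows section 8.2 to the letter need not report a pregnancy conceived two or six weeks after stopping, record its outcome or follow the child. Women of child-bearing potential are eligible, and section 1.1 notes that LAM in TSC mainly affects premenopausal women, so the case is not remote.

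What would be lost is information on pregnancy outcomes in a period that the protocol itself singles out, for a drug whose human reproductive risk it calls unknown.

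**Working it through.** No statistical figure is involved. The check sets the windows side by side, counting days from the last dose.

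| Rule | Source | Days covered after last dose |
|---|---|---|
| Contraception | 5.1, 7.3.1.1, 7.6.5.6, 8.2 | 1 to 56 (8 × 7) |
| Report of a patient's pregnancy | 8.2 | none stated |
| 12-month newborn follow-up | 8.2 | none stated |
| Partner pregnancy outcomes | 8.2 | no time limit stated |
| AEs and all SAEs | 4.4, 6.7.4, 8.1 | 1 to 28 |
| SAEs suspected to be drug-related | 4.4, 6.7.4, 8.1 | 29 to 84 |
| Safety contacts | 6.7.4 | visit at day 28, contact at day 84 |

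**Step 1: the gap.** The two patient rules in 8.2 cover 0 of the 56 days for which contraception is required.

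**Step 2: is the wording deliberate?** The patient sentence concerns a patient who is on drug, while the partner sentence concerns men who took it. Within one section, the time limit is narrower for women who took the drug themselves than for partners of men who took it.

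**Step 3: does SAE reporting fill the gap?** Section 7.6.1 does not list pregnancy as an SAE criterion. It does list congenital anomaly or birth defect, but timing limits what that catches. For a conception on day 1, day 84 falls 84 − 1 = 83 days later. For a conception on day 56, it falls 84 − 56 = 28 days later. When the SAE window closes, such a pregnancy is therefore at most 83 days past conception, and an ordinary birth comes after it. Only the pregnancy form and newborn follow-up in 8.2 reach the birth, and their wording leaves these pregnancies out.

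**Step 4: is the site still in contact?** Yes. The day-28 visit falls inside the contraception period and the day-84 contact comes 84 − 56 = 28 days after it ends.

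**Step 5: testing.** For a woman who stops drug before the study ends, one statement ends her tests at discontinuation and the other continues them monthly to the end of the study. Both stand in section 7.3.1.1. The final serum test does not settle the matter: Tables 7-1 and 7-2 mark it at end of treatment and at visit 780, and the protocol does not say which reason for stopping leads to which. End-of-treatment evaluations are done within 1 week of stopping (section 6.7.4), whereas the visit 780 form may be completed long after drug is stopped. No test is clearly fixed within or at the end of the 8 weeks.

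**The case against.** The strongest reply is that post-dose capture is not nil. All SAEs are collected to day 28 and suspected-related ones to day 84. Hospitalisation and medically significant events count as SAEs, and section 8.2 wants any SAE during pregnancy on the SAE form, with no explicit on-drug limit. A complicated pregnancy may well be seen. This stands, and it narrows the gap to pregnancies without a reportable SAE and to births after day 84.

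Second, the protocol gives no reason for the 8 weeks. Section 1.4.4 puts the terminal half-life at about 30 hours, so five half-lives are 5 × 30 = 150 hours, about 6 days. This also stands. The documents do not support calling every conception in the period drug-exposed. The argument here needs only the protocol's own contraception period.

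Third, the partner rule is wider in time but not in every respect: it needs the mother's consent and sets no separate 24-hour deadline. That is correct, and the comparison is used here for timing only.

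Fourth, the monthly-testing sentence could be read as saying only that testing applies in both core and extension phases, which would remove the contradiction. That reading is possible, but the sentence names the end of the study, and sites should not have to guess.

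**Conclusion.** The point holds for reporting and newborn follow-up. As written, section 8.2 covers 0 of the 56 post-treatment days for which the protocol requires contraception. An uncomplicated pregnancy conceived in those days need not be reported, and the child need not be followed. This rests on reading the two trigger sentences literally and on SAE collection ending at day 84. The documents give no basis for estimating how many women would be affected.

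On testing, the finding is an internal contradiction about when it ends, and no more.

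A reader might infer more than the text supports:

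- **Testing simply stops with the drug.** A serum test is due at end of treatment or end of study, and one sentence requires monthly testing to study end. Whether tests are done in the 8 weeks is undetermined.
- **A conception in the last days on drug escapes reporting if found later.** It still began on treatment, and the 24-hour clock runs from learning of it, so 8.2 reasonably covers it.
- **Patients take the drug for 4 to 5 years.** In section 4.5 that figure is follow-up. Treatment can end earlier, for example at progression or for toxicity.

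This is a safety-reporting matter. It does not touch the primary analysis, power or type I error.

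**What to change.** In section 8.2, reword the on-drug condition in both the reporting sentence and the newborn sentence so that they also cover pregnancies conceived up to the end of the protocol's existing 8-week post-treatment contraception period. Apply the same 24-hour reporting, outcome collection and 12-month newborn follow-up. Ask about pregnancy at the existing 28-day visit and 84-day contact. The cost is protocol wording and a few more pregnancy forms and newborn follow-ups, with no new visit.

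Separately, the sponsor must reconcile the two end points for pregnancy testing across sections 7.3, 7.3.1.1 and 7.6.5.6 and the pregnancy-test footnotes to Tables 7-1 and 7-2, and state which reasons for stopping place the final serum test at end of treatment and which at end of study. Which testing schedule applies is for the sponsor to settle.
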